### Exposure variable and index dates

For reasons of patient confidentiality, Clinical Practice Research Datalink
contains year of birth rather than full date of birth. Therefore, age will be
calculated by subtracting the year of birth from 2014, and we will compare
patients whose age was in a small bandwidth (interval) above and below 75 years.
This bandwidth will be selected using standard cross-validation methods [31].

We will report the proportion of patients in each age group who received the
intended treatments. Since the policy ensures that the vast majority of patients
who are eligible for a named accountable general practitioner within 2014/15
will have received one by September 2014, treatment receipt will be based on the
presence of a recorded named accountable general practitioner within a 6-month
period (April 2014 to September 2014), using the Read code prescribed by the
General Medical Services contract (67DJ). Patients without a recorded named
accountable general practitioner by September 2014 will be regarded as untreated
patients, even if they received a named accountable general practitioner
subsequently.

All patients will be assigned an index date for the purposes of calculating
endpoints and covariates. For patients who are assigned a named accountable
general practitioner between April and September 2014, this will be the date at
which this was recorded. Patients who are not assigned a named accountable
general practitioner during this period will be randomly assigned an index date,
such that the distribution of index dates across months is the same as for those
patients who did receive one. Thus, all patients will have at least 6 months
follow-up within 2014/15, before the policy was extended to all patients
irrespective of age [39].

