### Study endpoints and covariates

Our primary endpoint will be the number of general practitioner contacts per head
over 6 months; this will include all appointment types (e.g. both surgery visits
and telephone calls). Secondary endpoints, also calculated over 6 months, will
be a measure of longitudinal continuity of care; the number of contacts with
general practitioners or practice nurses; numbers of referrals to specialist
care; and number of common diagnostic tests (e.g. blood pressure). There are
several measures of longitudinal continuity of care, which focus on the
concentration, dispersion, distribution or sequence of consultations [12,17]. The Usual Provider of Care index measures the proportion of
contacts with the general practitioner who is most commonly seen [17]. The Usual Provider of Care index is
widely used [11] and is more easily
interpreted than some of the other measures [12]. The Usual Provider of Care index was not chosen as the primary
endpoint, as this measure is only defined for the subgroup of study participants
with at least two general practitioner contacts during the study period. The
theory behind the intervention is such that a change to the number of general
practitioner contacts, referrals to specialist care or numbers of diagnostic
tests is more likely following an improvement to continuity of care. However, we
will analyse these endpoints regardless of the findings for the Usual Provider
of Care index, since it is theoretically possible that, for example, the letters
led to an increase in enquiries from patients without improvements to
continuity.

The following covariates will be calculated for all patients, using data recorded
prior to the index date: gender; ethnicity; socioeconomic score (attributed to
the patient according to their area of residence, and measured by deciles of the
Index of Multiple Deprivation 2010) [40];
number of long-term health conditions recorded prior to the index date; and
numbers of general practice contacts, referrals to specialist care, diagnostic
tests and hospital discharges in the 6 months prior to the index date. Long-term
conditions will be defined in accordance with the Quality and Out-comes
Framework. The data quality for the Quality and Outcomes Framework indicators is
enhanced as a result of these conditions forming part of the pay-for-performance
scheme for general practice [41].

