## Statistical methods

Our initial analysis (Table 1) suggests that
the proportion of patients receiving a named accountable general practitioner is
discontinuous at the threshold, but this will be confirmed on receipt of the data.
We will also confirm that, although we would expect a trend in certain covariates
across age, there are no discontinuities in these covariates at age 75. This
comparison will be done graphically and include all patients, regardless of actual
treatment assignment. We do not expect such discontinuities to occur, but if they do
exist, this would lead us to question the validity of our study design.

As mentioned previously, the proportion of patients receiving a named accountable
general practitioner is unlikely to jump from 0 to 100% at age 75. It will therefore
be appropriate to apply a fuzzy regression discontinuity design [31], by fitting four regression models. Two
models will relate the outcome to a polynomial function of age: one model will be
fitted for people whose age lies within the bandwidth below the threshold and the
other model for people within the bandwidth above the threshold. The final two
models have treatment assignment as their dependent variable rather than outcome.
All models will use ordinary least squares regression and include patients
irrespective of their actual treatment assignment. We will calculate the estimated
treatment effect as the difference between the predictions of the two outcome models
at age 75, divided by the difference between the predictions of the two treatment
models at age 75.

The analysis will have regard to the rounded nature of the running variable (i.e.
age), resulting from the use of year of birth rather than full date of birth. This
will exclude the use of very small bandwidths, and so we will use a larger interval
spanning several years and model any trend in the endpoints by age using parametric
approaches based on polynomial functions [42,43]. In the absence of
information on full date of birth, it will not be possible to establish for a given
patient born in 1939 what date they turned 75, and therefore which side of the
threshold the patient is at the index date. We will remove the risk of
misclassification by excluding all patients born in 1939 when fitting the regression
models and making a small extrapolation around age 75 [42]. A final consideration is that, when the running variable
is only observed at discrete points, discretisation bias can occur because a change

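### Receipt closes at September 2014 while outcome windows run to as late as March 2015, so receipt during follow-up can move the outcome jump but never the receipt jump; the net bias is probably a few percent and needs sensitivity runs

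*Protocol article*

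**What the plan says.** All references are to the protocol article.

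- **Receipt** (Exposure variable and index dates). Treatment is the "presence of a recorded named accountable general practitioner within a 6-month" period, April to September 2014, identified by Read code 67DJ. The reason given is that the great majority of eligible patients "will have received one by September 2014, treatment receipt will be based on the" record in that period. No figure is given. The rule for the rest is explicit: "Patients without a recorded named accountable general practitioner by September 2014 will be regarded as untreated patients, even if they received a named accountable" GP after that date.
- **Index dates** (same section). Recipients are indexed at the recorded date. Others get a random date, "such that the distribution of index dates across months is the same as for those" who received one. The section concludes: "Thus, all patients will have at least 6 months follow-up within 2014/15".
- **Outcome** (Study endpoints and covariates). "Our primary endpoint will be the number of general practitioner contacts per head", counted over six months.
- **Estimator** (Statistical methods). The outcome jump at age 75 is divided by the receipt jump at age 75. Age is 2014 minus birth year.
- **Births near the cut-off** (same section). "We will remove the risk of misclassification by excluding all patients born in 1939". The reason given is that their side of the threshold at the index date is unknown.

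**The concern.** The ratio estimates the complier effect only if eligibility changes outcomes solely through the receipt variable in the denominator. Two groups break that link.

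1. **Late recipients aged 75 and over.** A record made after September but inside the patient's own window can change that patient's contacts. The patient still counts as untreated. The divisor is too small and the effect is overstated in absolute size.
2. **Births in January-March 1940.** They are under 75 at every possible index date, so the 1939 exclusion keeps them in the below-75 fit. They can turn 75 before their window closes, but only if the index date is July or later. If they are then notified promptly, the fitted outcome below the cut-off moves towards the treated level and the outcome jump shrinks. 1940 is also the birth year nearest the cut-off, so it carries the largest weight in the extrapolation.

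The planned checks are placebo cut-offs, bandwidth, polynomial order and covariates. None of them varies the receipt definition or targets the 1940 cohort.

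**Working it through.** **Plan's own figures.** The plan gives no figure for late receipt. Table 1 gives 5,420/105,250 = 5.1% receipt at ages 70-74 and 67,770/84,931 = 79.8% at 75-79, a jump of 0.746. Table 1 is described as illustrative, from 2014 data whose months are not stated, with not all exclusions applied.

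**Assumptions.** L is the share of the 75-and-over side first recorded after September, taken as 2-20%. In the base case, index dates are even over April-September, late receipts are even over October-March, birthdays are even over the year, and the effect is proportional to exposed time.

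**Formula.** Estimated/true effect = (0.746 + L × e − w × c × 0.798) / 0.746, where

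- e is the mean share of the window that late recipients spend treated;
- c is the share of the 1940 cohort's person-time after the 75th birthday;
- w is the weight of age 74 in the below-75 fit extrapolated to 75.

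**Inputs in the base case.**

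- e: index date and late receipt are both uniform over six months, so the mean overlap is 1/6 = 0.167. Half of late recipients are recorded before their window ends.
- c: with t the months from 1 April to the index date, a January-March birthday falls inside the window only for t > 3. The share crossing is (1/6) × ∫₃⁶(t − 3)dt / 12 = (4.5/6)/12 = 6.25%. The person-time share is (1/6) × ∫₃⁶[(t − 3)²/2]dt / (12 × 6) = (4.5/6)/72 = 1.04%.
- w: linear over 5 years, 1/5 + (3 × 2)/10 = 0.80. Linear over 10 years, 1/10 + (5.5 × 4.5)/82.5 = 0.40. Quadratic over 5 years, 1.80.
- 0.798 assumes that 1940 births reach the full receipt rate at their birthday. Using the increment 0.746 instead lowers the 5-year linear term from 0.0066 to 0.0062.

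**Base-case results (estimated/true).**

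| L | Linear, 5 years | Linear, 10 years | Quadratic, 5 years |
|---|---|---|---|
| 2% | 0.996 | 1.000 | 0.984 |
| 5% | 1.002 | 1.007 | 0.991 |
| 10% | 1.013 | 1.018 | 1.002 |
| 20% | 1.036 | 1.040 | 1.025 |

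Taken separately, late receipt adds 0.4% to 4.5%. The 1940 cohort subtracts 0.4% to 0.9% with linear fits and 2.0% with the quadratic.

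**Other index-date patterns, exposure-proportional effect, L = 2-20%.**

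- All in April-June: the 1940 term is zero and the ratio is 1.001-1.011.
- All in July-September, linear: 0.990-1.069.
- All at the end of September: 0.96-1.11 linear, and 0.89 at the low end with the quadratic.

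**Effect occurring at notification, even dates.** Replace e by 0.50 and c by 0.0625. At L = 2% (linear, 5 years): (0.746 + 0.010 − 0.040)/0.746 = 0.96. At L = 20% (linear, 10 years): (0.746 + 0.100 − 0.020)/0.746 = 1.11.

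**Own-window flag as treatment variable.** Consider late recipients only, with an exposure-proportional effect and the jump rounded to 0.75. The ratio is (0.75 + 0.167L)/(0.75 + 0.5L) = 0.98, 0.96, 0.92 at L = 5%, 10%, 20%. Under the September rule it is 1.01, 1.02, 1.04.

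**The case against.** The cut-off is deliberate, disclosed and reasoned, and nothing in the documents shows the reason to be wrong. If nearly all eligible patients were recorded by September, L is small and so is the error. Late recipients are exposed for only part of their window, or for none of it. Only September index dates reach March 2015. The two biases oppose each other and partly offset. A 4% error on the 0.25-contact target effect is 0.010 contacts, against a standard error of 0.25/3.24 = 0.077 implied by 90% power in a simple two-group comparison. All of this stands and limits the size of the point. It does not remove the mismatch, and the offset depends on unrelated quantities (late uptake, index-date timing, polynomial order).

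A reader might take the 20% not notified at ages 75-79 in Table 1 as the late share. The table does not support that: its months are unstated, so some late recipients may already be in the 80%, and the 20% includes patients never notified. The Study design section itself expects that some older patients might not receive a named GP.

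A reader might also infer inflation of up to 24%. That needs L = 20%, meaning nobody aged 75 and over is left without a named GP, together with every late receipt in October and the full effect at notification: (0.75 + 0.20 × 0.92)/0.75 = 1.24. An effect at notification is plausible on its own, since the protocol mentions letters prompting enquiries. The combination is not supported.

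**Conclusion.** The mismatch is real and no planned check detects it. Its likely size is modest: about -0.4% to +4% net for L = 2-20% under even dates, an exposure-proportional effect and linear fits. It is larger, roughly -4% to +11%, if the effect occurs at notification with linear fits. Index dates clustered in August-September or a quadratic fit also widen it. L and the index-date distribution are assumptions, because the documents give neither. The 1940 component also assumes notification soon after the 75th birthday, which is inferred from eligibility at 75 and not stated.

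Two stronger readings fail. The documents do not show that these patients are treated throughout follow-up while counted as untreated, because exposure covers part of the window at most. Nor can the mismatch produce a false positive: it multiplies an existing effect, so if named GPs have no effect, the expected outcome jump remains zero.

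**What to change.** Keep the September rule for the main analysis, and add to the specification tests in Statistical methods:

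1. The ratio with receipt in the treatment models defined as any 67DJ record within the patient's own six-month window. This suits an effect at notification.
2. The ratio with receipt replaced by the fraction of that window after the 67DJ record. This suits an effect proportional to exposure.
3. A run that drops birth year 1940 as well as 1939.

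Report receipt after September by birth year, which replaces the assumed L with data. Reword the misclassification sentence to say that excluding 1939 settles the side of the threshold at the index date only, not during follow-up.

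**Cost.** The runs need 67DJ dates to the end of each window and two redefined variables. The binary own-window flag counts very late receipt as full treatment and can understate the effect by about 2-8% at L = 5-20%, so it should not replace the main definition. Dropping 1940 costs precision. For a linear fit on five birth years, the below-side variance factor rises from 1/5 + 9/10 = 1.1 to 1/5 + 16/10 = 1.8 if a further year is added to keep five, or to 1/4 + 3.5²/5 = 2.7 if only four remain.

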care have been conducted within specific localities, which can limit the
generalizability of study findings [4,16,17,21,22,23]. However, in 2014,
the Department of Health reformed the contract for general practices in England to
require that all patients aged 75 or over be appointed a named general practitioner
with specific responsibilities for care coordination [24]. This policy provides an opportunity to evaluate the effect
of a national initiative on continuity of care and so relates variation in
effectiveness to differences in the local context [25]. Although a recurrent concern with ‘top-down’ reforms is
that changes might not have the active buy-in of local practitioners [26], with few exceptions [27] these are seldom evaluated. This is an important gap in the
literature as contractual reform is one of the few policy-making levers that promise
direct impact.

Estimating the effect of interventions aimed at providing more integrated or
continuous care is often challenging because studies are typically not randomised
[21,28]. Thus, intervention and control groups might differ at baseline and,
unless outcomes are accurately adjusted for these differences, inferences can be
biased [29]. Studies often use regression
adjustment or propensity score matching, but these methods assume that all relevant
baseline characteristics have been observed, which may be implausible [30]. Regression discontinuity methods avoid
having to make this assumption and are appropriate where eligibility for an
intervention changes sharply at a predefined threshold [31]. The key insight is that patients just above and below the
threshold should have similar baseline characteristics. Therefore, any discontinuity
in the outcome variable at the threshold can be attributed to differences in the
treatments received. Regression discontinuity designs have been shown to replicate
the results of randomised controlled trials [32] and, although underutilised in health services research, are well
established in the economics literature [31,33,34].

The article describes the design of a regression discontinuity study to assess
whether the national policy to introduce named accountable general practitioners led
to changes in the longitudinal continuity of care and to relate these to the
characteristics of general practices.

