## Methods

### Reform to the general medical services contract in England

The 2014/15 General Medical Services contract introduced a requirement for
general practices in England to offer patients aged 75 or over a named
accountable general practitioner, who should provide longitudinal continuity of
care within the general practice and be accountable for coordinating care to
meet the patient’s health and social care needs. In particular, the named
accountable general practitioner should ensure that patients receive all
appropriate services and work with relevant associated healthcare and social
care professionals to deliver a multidisciplinary care package [24,35]. The contract requires that the practice notify the patient of their
named accountable general practitioner, usually by letter, and make a reasonable
effort to accommodate patient preferences about the choice of general
practitioner. However, patients are not prevented from seeing any other general
practitioner in the practice [36]. The
2014/15 GMS contract changes led to a step change (discontinuity) in the
percentage of patients receiving a named accountable general practitioner, which
increases from around 5% to around 80% near age 75 (Table 1).

**Table 1 T1:** Preliminary analysis of data from Clinical Practice Research Datalink
showing that the requisite discontinuity exists in the data.

	Patients aged 70–74 (%)	Patients aged 75–79(%)

Notified of named accountable general practitioner	5420 (5%)	67,770 (80%)
Not notified of named accountable general practitioner	99,830 (95%)	17,161 (20%)
Total	105,250	84,931

*Note:* Based on preliminary analysis of Clinical
Practice Research Datalink data. Figures are illustrative as this
analysis was based on 2014 data and not all exclusion criteria were
applied.

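### Named-practitioner receipt that is late or uncoded can move the outcome jump at 75 but is left out of the treatment jump, so the ratio may be modestly biased

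*Protocol article*

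**What the plan says.** All references are to the Protocol article.

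- **Exposure variable and index dates.** Treatment means a recorded named practitioner within a 6-month "period (April 2014 to September 2014), using the Read code prescribed by the" contract. Anyone without that record by the end of the window joins the untreated "patients, even if they received a named accountable general practitioner" afterwards. The reason given begins "Since the policy ensures that the vast majority of patients" and goes on to say that eligible patients will have been covered by September 2014. No figure supports it.
- **Same section, index dates.** A treated patient's index date is the date of the record. Untreated patients receive random dates, "such that the distribution of index dates across months is the same as for those" who were treated. The section adds: "Thus, all patients will have at least 6 months" of follow-up within 2014/15. Endpoints are counted over 6 months.
- **Statistical methods.** All patients stay in the models whatever they received. The treatment effect is the difference between the two outcome predictions "at age 75, divided by the difference between the predictions of the two treatment" models. The specification tests vary the placebo thresholds, the bandwidth, the polynomial order and the covariates. None varies the definition of treatment.
- **Introduction.** The aim is to assess "whether the national policy to introduce named accountable general practitioners led" to changes in longitudinal continuity.

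**The concern.** Index dates fall between April and September 2014, so follow-up ends between October 2014 and March 2015. A patient first recorded in, say, November can be exposed for part of the counted period and still be coded untreated. A patient given a named practitioner without the prescribed code can be exposed for all of it.

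The fuzzy ratio has a complier interpretation only if eligibility affects outcomes through the treatment as measured. Exposure that the coding omits breaks that condition: its effect is in the numerator and its receipt is not in the denominator. The estimate is then scaled by an amount that depends on when and how practices recorded the code.

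This matters for the reported size of effect, since the plan treats a 5% change in contacts as meaningful (Required sample size). It could also matter for the practice-level regressions (Subgroup analyses) if recording differs between practices.

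**Working it through.** **Inputs from Table 1**
- Aged 70–74: 5420/105,250 = 5.1%. Aged 75–79: 67,770/84,931 = 79.8%. These reproduce the stated 5% and 80%.
- Coded treatment jump p = 0.798 − 0.051 = 0.746.
- No record at 75–79: 17,161/84,931 = 20.2%.
- The table's note calls the figures illustrative, from 2014 data, with not all exclusions applied. It gives no cut-off month.

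**Inputs assumed, because the document gives none**
- d = uncounted receipt just above 75 minus uncounted receipt just below: 2, 5, 10 or 20 points.
- f = average share of the 6-month follow-up that lies after the uncounted receipt.
- The effect accrues in proportion to exposed time.

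**Formula.** Let T be the effect of a named practitioner held for the full 6 months. The outcome jump is T(p + f·d). The planned ratio is T(p + f·d)/p = T(1 + f·d/p), so the relative bias is f·d/p.

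**Values of f**
- *Uniform dates.* Let X be months from April to the index date and Y months from October to late receipt, both uniform on 0 to 6. Exposed time is max(0, X − Y), with mean 1 month, so f = 1/6. About half of late recipients have any overlap.
- *Index dates only in April–June.* Mean exposed time is 0.25 month, so f = 1/24.
- *All late receipt on 1 October, uniform index dates.* Mean exposed time is 3 months, so f = 1/2.
- *Uncoded receipt held throughout follow-up.* f = 1.

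**Bias of the planned ratio, f·d/p with p = 0.746**

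| d (points) | f = 1/6 | f = 1/2 | f = 1 |
|---|---|---|---|
| 2 | 0.4% | 1.3% | 2.7% |
| 5 | 1.1% | 3.3% | 6.7% |
| 10 | 2.2% | 6.7% | 13.4% |
| 20 | 4.5% | 13.4% | 26.8% |

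Example: (1/6 × 0.20)/0.746 = 4.5%. With f = 1/24, the 20-point case gives 1.1%.

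**If Table 1 already includes late receipt**, the coded jump is 0.746 − d. At f = 1/6 the bias is 1.2% for 5 points and 6.1% for 20. At f = 1/2 and 20 points it is 0.10/0.546 = 18.3%.

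**Direction.** If uncounted receipt is equal on both sides, d = 0 and there is no bias. With 5 points above and 10 below, at f = 1/6, the ratio is 1 − (1/6 × 0.05)/0.746 = 0.989 of the true effect.

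**No effect.** If T = 0, the ratio is zero whatever d and f are.

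**Alternative codings of late recipients**
- *Counted as fully treated:* the ratio becomes T(p + f·d)/(p + d). At f = 1/6 this is 0.948T for 5 points and 0.824T for 20, an understatement of 5% to 18%.
- *Counted by share of follow-up exposed:* the ratio becomes T(p + f·d)/(p + f·d) = T.

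**The case against.** **The plan gives its reason.** If nearly all eligible patients were recorded by September, d is small and so is the bias. This stands. But no rate is given, and the statement does not address receipt without the code.

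**The direction is not shown.** This also stands. The 1939 birth year is excluded, so 1940 is the nearest cohort below the threshold. Those born in January–March 1940 reach 75 before April 2015 and could add late receipt on the lower side. More late receipt above 75 is the natural expectation, because the contract obliges practices to cover that group, but it remains an expectation.

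**A reader might infer inflation of up to 27%.** The documents do not support that for late receipt. It needs all 20 points without a record to be exposed for the whole of follow-up, whereas receipt from October can reach only its later part. The 20% also includes patients who never had a named practitioner, and they cause no bias.

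**A reader might also infer that the outcome jump does not depend on coding.** It does: treated patients' index dates are the code dates, and untreated dates are drawn to match. What the jump avoids is the incomplete denominator.

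**The complier effect is a deliberate choice.** The abstract asks for the effect of named practitioners, and Study design and the limitations both describe the complier restriction. That is legitimate, so the ratio should stay. The Introduction nevertheless also asks about the policy, and the jump answers that question.

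**An article may leave sensitivity runs to a fuller document.** That is fair for detail. Here, however, the article itself fixes the coding rule, the estimator and a list of checks.

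**Conclusion.** The point holds as a conditional and mostly modest bias. The coding rule lets uncounted receipt affect the numerator but not the denominator, and the ratio overstates the complier effect if that receipt is commoner just above 75.

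- **Late receipt alone:** about 0.4% to 4.5% for 2 to 20 points under uniform dates, and up to about 13% if all of it came on 1 October. The figures are somewhat higher if Table 1 already includes late receipt.
- **Uncoded receipt:** about 7% at 5 points and 13% at 10 if exposure lasts throughout follow-up. The document gives no rate, so these are illustrations.

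The figures rest on Table 1 as a stand-in for September status and on an effect proportional to exposed time. If the effect came all at once on notification, the relevant share under uniform dates would be the half of late recipients with any overlap, which gives the f = 1/2 column.

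The bias multiplies the effect, so it does not create an effect where there is none, and the test of no effect is essentially unaffected.

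**What to change.** 1. Report the outcome jump at 75 as the effect of eligibility (the policy effect), alongside the ratio as the complier effect. State that the outcome windows still depend on coded index dates.
2. Tabulate receipt recorded after September 2014 by age on both sides of 75. This tests the plan's justification and shows the sign of d for recorded late receipt.
3. Add a sensitivity analysis in which the dependent variable of the treatment models is the share of each patient's own 6-month follow-up after recorded receipt. It equals 1 for patients treated under the present rule and lies between 0 and 1 for late recipients.
4. Show coding as treated on any receipt within follow-up only as the opposite bound. It ignores partial exposure and errs towards zero.

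Uncoded receipt cannot be recovered this way and should be stated as a limitation.

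The cost is one extra run of the treatment models and one table. The outcome jump is already computed as the numerator.

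### The index date depends on whether a named GP was recorded, so the start of the outcome window is not set in the same way on the two sides of age 75

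*Protocol article*

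**What the plan says.** The section Exposure variable and index dates gives the index date its role: "All patients will be assigned an index date for the purposes of calculating" endpoints and covariates. Two rules then apply.

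- Treated patients: for those assigned a named "general practitioner between April and September 2014, this will be the date at" which the assignment was recorded.
- Untreated patients: anyone not assigned a named "general practitioner during this period will be randomly assigned an index date", drawn "such that the distribution of index dates across months is the same as for those" who did receive one. No matching within practice is stated.

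A patient without a recorded named "accountable general practitioner by September 2014 will be regarded as untreated", even if one is recorded later.

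Under Study endpoints and covariates: "Our primary endpoint will be the number of general practitioner contacts per head". The count runs for six months, and telephone consultations are included as well as visits to the surgery. Whether contacts on the index date itself count is not stated. Prior contacts, referrals, tests and discharges are counted over the six months before the same date.

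The section on the contract reform says that the share with a named GP "increases from around 5% to around 80% near age 75". It also says that patients are normally told by letter.

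**The concern.** A regression discontinuity attributes a jump in the measured outcome at 75 to treatment. That requires everything else about the outcome, including how it is measured, to be smooth there. Here the start of the window follows receipt, and receipt is the variable that jumps. A code entered during a consultation opens the window at a contact; a randomly drawn date usually does not. If that happens often enough, the contact count differs across 75 with no effect of the named GP.

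Matching on month equalises the calendar mix, and all windows have the same length. Neither equalises the type of event that opens the window. Including patients irrespective of actual treatment does not help either, because the mix of the two rules differs by age side.

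The Subgroup analyses section estimates an effect in each practice. If a practice coded all its patients in one month while its untreated patients received dates from the overall distribution, season would differ between the two groups within that practice.

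**Working it through.** **Inputs from the protocol**

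- Treated share (Table 1): 5,420/105,250 = 5.1% at ages 70–74 and 67,770/84,931 = 79.8% at ages 75–79. The difference is 0.746, which reproduces the rise from about 5% to about 80%. The protocol calls these figures illustrative.
- Target (Required sample size): 5% of 5 contacts = 0.25 contacts; SD 6.
- Estimator (Statistical methods): outcome jump at 75 divided by treatment jump at 75.

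**Assumption not in the protocol.** A share q of treated patients, equal on both sides of 75, has the code entered at a GP contact that counts in follow-up.

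**Bias with no true effect**

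- Mean above 75: μ + 0.798q. Mean below: μ + 0.051q.
- Outcome jump: 0.746q. Ratio: 0.746q / 0.746 = q contacts.

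| Assumed q | False outcome jump | False ratio estimate | Share of the 0.25 target |
|---|---|---|---|
| 5% | 0.037 | 0.05 | 20% |
| 10% | 0.075 | 0.10 | 40% |
| 25% | 0.187 | 0.25 | 100% |

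A slightly finer version allows for the contacts expected on any one day. Taking six months as 182 days, that is 5/182 = 0.027, so the bias is 0.973q: 0.049, 0.097 and 0.243. A gamma-Poisson simulation with mean 5 and SD 6 gave 0.09 for q = 10% and 0.25 for q = 25%.

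**Rough effect on false positives.** In a plain two-group comparison with the stated 24,212 per group, SE = 6√(2/24,212) = 0.0545. The 5% rejection rate then becomes 10.5%, 28% and 93% for the three values of q. This is only a scale. Polynomial fits extrapolated to 75 have a larger standard error, which lowers these rates. Also, the two-sample formula 2(1.960 + 1.282)²(6/0.25)² gives about 12,105 per group, so 24,212 fits the total of both groups. That is a separate matter and does not alter the bias.

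**If index-day contacts are excluded.** With contacts independent in time, the simulated bias is about 0. If contacts cluster, for example 0.5 extra follow-up contacts after a coding contact (assumed), the bias is 0.5q: about 0.12 at q = 25%, and 0.25 at q = 50%.

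**Would the planned checks show it?**

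- Non-discontinuity ages: receipt does not jump there, so neither does the anchor. These can look clean.
- Bandwidth and polynomial order: same outcome windows, same anchor.
- Covariate adjustment: pre-index counts do not contain an index-day contact.
- Covariate continuity: if coding falls within a spell of clustered contacts, prior contacts could jump at 75, and the protocol says that a covariate jump would call the design into question. A lone index-day contact leaves no trace.

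**The case against.** The strongest reply is that the size rests wholly on q, and the text points towards a small q. Notification is usually by letter, a mailing is not a consultation, and batch coding would put q near zero. The headline figures also need index-day contacts to be counted, a detail that an article may leave to the full protocol. Both points stand: the mechanism is in the text, but its size is not.

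On practices, the same practices supply patients on both sides of 75. If practice and season effects are additive, the mismatch cancels in the pooled estimate. That also stands, and confines the practice point to the practice-level estimates and the regression built on them.

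Three stronger readings are tempting but not supported:

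- That the covariate check is spoiled. Gender, ethnicity and deprivation hardly depend on the index date, and the prior-contact check can reveal clustering.
- That late recipients, treated in follow-up but classed as untreated, inflate the ratio by a calculable percentage. Late means after September, so recording halfway through six months is possible only for index dates after June. Table 1 also states no September cut-off, so its un-notified 20% is not a count of late recipients.
- That the bias imitates a hypothesised rise in contacts. An index-day contact does push the estimate upwards, but the plan tests a two-sided change and hypothesises no increase.

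**Conclusion.** The concern holds as a design weakness of unknown size. The index-date rule depends on receipt, receipt jumps by about 75 points at 75, and so the anchoring of the outcome window is not smooth at the threshold. The bias in the ratio is about q contacts if index-day contacts count, and about zero if they do not and contacts are not clustered. A bias as large as the 0.25-contact target needs roughly one treated patient in four to be coded at a counted contact; the documents give no evidence for or against that share. A larger sample does not reduce the bias, and the planned checks cannot be relied on to show it. A reader might infer that a false effect is to be expected; the protocol supports only that one is possible and is not ruled out. The case for change is that the path can be closed cheaply.

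**What to change.** - Set the index date for all patients by one rule that ignores receipt: a common calendar date, or dates drawn for everyone from the same distribution. For the practice-level analysis, draw them within practice.
- Measure prior-utilisation covariates before April 2014.
- Keep the current rule as a sensitivity analysis, and exclude index-day contacts in any analysis that starts at the recording date.
- Report the reduced-form jump at 75 beside the ratio. It is already the numerator and, once the window ignores receipt, it does not depend on how or when receipt was coded.

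This uses the same data, but it has a price. The window no longer opens at each patient's notification, so some early reactions to letters, which the protocol wants to capture, may be diluted or missed. If October 2014 to March 2015 is chosen as the common window, patients first recorded after September are exposed during follow-up while classed as untreated. The choice of date should weigh these two losses, and the report should state what the resulting estimate refers to.
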